## Abstract

**Background:**

A growing body of evidence suggests that early life health and developmental outcomes can be improved through parental support programs. The objective of this project was to test the feasibility, impact, and relative cost-effectiveness of an adapted “Reach Up and Learn” program delivered through home-visiting programs as well as through center-based parenting groups on child health and development in the municipality of Boa Vista, Brazil.

**Methods:**

A randomized, stepped-wedge design was used to roll out and evaluate the two parenting platforms in Boa Vista municipality. A total of 39 neighborhoods with a high Neighborhood Vulnerability Index were selected for the study. For the first phase of the program, nine neighborhoods were randomly selected for home visits, and two were randomly selected for the center-based parenting groups. In the second phase of the program, 10 neighborhoods were added to the home-visiting program, and eight were added to the center-based program. In the final phase of the program, the remaining 10 control areas will also be assigned to treatment. Study eligibility will be assessed through a baseline survey completed by all pregnant women in the 39 study areas. Pregnant women will be eligible to participate in the study if they are either classified as poor, were under age 20 years when they became pregnant, or if they indicate to have been exposed to domestic or sexual violence. To assess program impact, an endline survey will be conducted when children reach age 2 years. The primary study outcome is child development at age 2 years as measured by the PRIDI instrument. Secondary outcome will be infant mortality, which will be assessed linking municipal vital registration systems to the program rollout.

**Discussion:**

This trial will assess the feasibility and impact of parenting programs rolled out at medium scale. The results from the trial should create evidence urgently needed for guiding Brazil’s national Criança Feliz program as well as similar efforts in other countries.

**Trial registration:**

ClinicalTrials.gov, ID: NCT03386747. Registered on 13 December 2017. All items of the World Health Organization Trial Registration Data Set are available in this record.

## Background

Brazil has made remarkable progress with respect to child nutrition and child survival over the past decade, with particularly impressive results in large urban areas. Infant mortality has dropped by roughly 50% since 2000 to 14 deaths per 1000 births across the country [1]. Most of the remaining mortality occurs during the neonatal period. More than 25,000 newborns are estimated to die each year within the first 28 days of their life in Brazil, with most deaths occurring in the first 7 days after birth. Previous studies suggest that one of the most effective ways to prevent such deaths is home-visiting programs, which support mothers in the first weeks of their infant’s lives, promote breastfeeding and kangaroo-mother care, and ensure appropriate medical care when needed [2–6]. From a child health and development perspective, the best outcomes have generally been achieved when continued support was provided to mothers from pregnancy throughout the first years of children’s lives. A nurturing and stimulating environment sensitive to maternal needs as well as the child’s health, nutritional and emotional needs is not only essential for healthy development but can also mitigate harmful effects of risk factors related to poverty and lack of parental resources [7–17].

Parental programs to promote nurturing environments have been successfully implemented in a range of low- and middle-income countries, including UNICEF’s *Care for Child Development (CCD)* framework, Jamaica’s *Reach Up and Learn* program, *Early Head Start* in the USA and the UK’s *Sure Start* [9, 18–22].

Brazil has successfully implemented its “family health strategy” – a health-focused home-visiting program coordinated by primary care units – since 2006 [23–25]. In 2016, the government passed the “Criança Feliz” law to further increase the support provided to vulnerable families [26]. Even though the program foresees home visits to all vulnerable families, there is very little guidance on how such programs should be implemented in Brazil, and what kind of content should be promoted.

In this project, we assess the scalability of a locally adapted version of an early childhood program previously developed in Jamaica. Between 2014 and 2016, the Jamaican “Reach Up and Learn” curriculum was adapted to the Brazilian context and tested through a small randomized trial in São Paulo (ClinicalTrials.gov, ID: NCT0270400). The content, delivered through fortnightly home visits, comprises parenting-skill tips as well as child stimulation activities supported with basic toys, addressing motor, social emotional, and cognitive development and language for families with children aged from 9 to 36 months.

While the reach of this program was not universal in this original trial, the estimated impact on participating mothers was large, and the program was well received at the local level (manuscript with main results under review). While this curriculum was delivered through home visits in the original study in São Paulo, recent evidence from Bangladesh [6] suggests that similarly positive impacts can be achieved through center-based parenting groups that are substantially cheaper from a logistical perspective.

Given this and given also that the municipality had previously invested in a center-based model, it was decided to test both delivery platforms within this project. Given the relatively high burden of neonatal mortality in the study area, we also decided to start the intervention earlier. By enrolling pregnant women at the beginning of their third trimester, the revised intervention program aims to improve support for mothers during the antenatal and neonatal periods with the ambition to increase health service utilization and reduce the risk of adverse birth outcomes. Figure 1 presents the theory of change through which the curriculum may improve child survival and development.

**Fig. 1 Fig1:**
[figure not shown]
Theory of change

### Objectives

The objective of this study is to rigorously assess the impact of an extended version of the previously tested and validated parenting curriculum on child survival and development in Boa Vista municipality. Through a three-arm trial, we will assess home visits through child development agents (intervention 1) as well as center-based parenting groups (intervention 2) relative to a randomly selected control group. Through a stepped-wedge rollout approximately one third of communities will receive the intervention in phase 1 of the rollout; in phase 2 of the program, two thirds of communities will be selected for interventions. All areas will receive interventions in the last phase of the program.

The specific study objectives are:
To evaluate the effect of home- and center-based parenting programs on child survival and developmentTo assess the impact of both programs on parenting behavior and practicesTo evaluate the implementation processTo estimate program cost and cost-effectivenessTo assess relative program, reach among extremely poor and immigrant populationsTo assess program spillover on older siblings in the household

### Trial design

The study was designed as a stepped-wedge, cluster randomized controlled trial with three arms. Arm 1 represents intervention delivered through fortnightly home visits; Arm 2 consists of the same content delivered through fortnightly center-based group meetings; Arm 3 is the control group.

To avoid contamination, neighborhoods were used as units of randomization. All 53 neighborhoods in Boa Vista were classified according to the municipality vulnerability criteria. Only neighborhoods classified as B (medium vulnerability) and C (high vulnerability) will be targeted by the program. As of 2017, 42 neighborhoods were in this category.

Three neighborhoods had either existing home-visiting programs or other planned interventions, and were excluded from the study, leaving a final study sample of 39 neighborhoods. Figure 2 presents the neighborhoods vulnerability distribution.

**Fig. 2 Fig2:**
[figure not shown]
Neighborhood Vulnerability Index

From a programmatic perspective, the *Survive and Thrive in Brazil – The Boa Vista Early Childhood Program* eventually aims at providing support to all children born in the municipality of Boa Vista from the end of the second trimester of pregnancy until the children reach age 3 years. This program was designed to closely align with the national “Criança Feliz” program (Legal Framework of Early Childhood, Law 13.257/2016) [23], which will also provide partial funding for this initiative.

## Methods

### Study setting

The city of Boa Vista has a population of approximately 330,000 people, with, 22,377 families (~ 30%) currently receiving or enrolled in social cash transfers under the Bolsa Familia Program, very similar to the national average (35% of the population) [27]. According to the municipality health secretariat, infant mortality rate is estimated at 14.2 per 1000 live births, with 21% of births by teenage mothers and 11% of infants born preterm [28].

### Eligibility criteria

Study eligibility is restricted both spatially and at the individual level. As mentioned in the “Study design” section, the scale-up targets only vulnerable neighborhoods. Boa Vista social services classify all neighborhoods based on literacy rates, average per capita income (less than one quarter of the minimum wage), access to water, sanitation, sewage systems, and electricity into A (low vulnerability), B (medium vulnerability), and C (high vulnerability) areas. Out of the 55 neighborhoods in Boa Vista, 12 were classified as “high socioeconomic status” (A), 14 were classified as “low vulnerability” (B), and 29 were classified as “high vulnerability” (C). The study was restricted to the 43 B and C areas^1^.

Within all target areas, all pregnant women as well as women with children under the age of 1 year are eligible for the program as long as they are either poor, were under the age of 20 years at the time of conception or were ever exposed to domestic or sexual violence.

### Interventions

#### Home visit arm (Arm 1)

The intervention will be delivered during fortnightly home visits with the presence of the child and at least one of the main caregivers (the program focuses on the mother, but ideally with paternal participation or any other family member who routinely spends time with the child). The home-visiting curriculum is divided into three main modules: (1) the pregnancy module: this module is designed to make mothers aware of pregnancy danger signs, to encourage adherence to antenatal care (attendance, performing exams, and supplementation), to improve bonding and positive parental practices and to prepare women for breastfeeding; (2) the neonatal module: comprises three home visits during the baby’s first month of life. One visit during the first week, a second visit at 15 days and the third visit at 28 days. The primary focus of these visits is babies’ health, breastfeeding and bonding; and (3) the child module for ages 2–36 months. Each home visit has three or four play activities to address child development domains (gross motor, fine motor, language, cognitive development, and social-emotional development). A recycled-materials toy kit is used to support these activities. Visits take in average 45 min; after demonstrating and practicing each activity with the caregiver, the visitor leaves the toys, and mother/caregiver is encouraged to play and interact with the child in the 2-week interval between the visits. Activities are age-appropriate, and toys and learning materials are exchanged for a new set at each visit. Home visits will be conducted by newly hired and trained child development agents, who will be tasked to complete 60 home visits per month (three visits per workday), supporting 30 families.

#### Group-meeting arm (Arm 2)

Group meetings are designed to deliver essentially the same content. Meetings are held fortnightly at the CRAS center (Social Services Centers) for groups of eight mothers and their children, other members of the family can participate as well. Groups are formed with participants at a similar stage of gestation or with children of similar age. Group composition remains fixed to increase bonding over time. The only difference between the center and the home-based curricula is the number of activities per session: due to the larger number of participants, the number of activities is reduced to two at the centers. The neonatal module is also reduced to one or two sessions since we do not expect mothers to attend the sessions during the first 2 weeks of the babies’ lives. Group moderators will be hired by the project and will be tasked to schedule three age-group-specific 1-h and 30-min sessions each day.

Program teams will be based at the seven regional social service units (CRAS) and will deliver the intervention according to the services’ coverage area. Group meetings will be held at the centers, where a meeting room will be fully dedicated to the project for ease of access to mothers since the rooms are distributed within the more vulnerable areas.

Attendance at the sessions, dropouts and refusals will be registered in the intervention logs and monitored by the team on a monthly basis. In order to improve adherence, if a participant skips three consecutive sessions, she will be contacted by the delivery team supervisor to understand the reasons and eventual problems that need to be addressed to continue participation. The dropout log registers the participants’ motives for discontinuity and, depending on these, the supervisor can also contact the participant to revert dropout.

#### Control group (Arm 3)

Pregnant women living in the control-group-allocated neighborhoods will receive the regular public services provided by the municipality. In terms of health care, they will receive primary, secondary and tertiary care through the primary care units and hospitals run by the municipality or state secretariat. They will also have access to the regular social services provided by the Social Services Units and to other social (and cash transfer) programs such as the Bolsa Família.

### Modification of interventions or protocols

After the trials have started, there will be no special criteria for discontinuing or modifying the allocated interventions. The research group will monitor, on a monthly basis, protocol-adherence aspects such as group allocation, participation, logs, and other registry instruments and will participate in the weekly delivery team meetings and supervise home visits and group meetings.

No protocol amendments are expected during the trial but the private investigator (PI) will notify funders, the municipality and the Institutional Review Board (IRB) if any changes should be needed. Any deviations from the protocol will be documented using a breach report form and the protocol will be updated in the clinical trial registry.

### Adherence

Program rollout will be closely monitored by the Steering Committee. Before the trial launch, the municipality agreed not to deliver similar concomitant interventions for this population in the selected neighborhoods. To ensure that this will not happen in practice, the research group will collect information on other social program participation.

### Concomitant and post-trial care

Implementing the strategies of the ECD intervention (groups meeting and home-visiting) will not require alteration to usual care pathways (including use of any medication). Standard medical and child support care will be available to all study arms throughout the trial. There is no anticipated harm and compensation for trial participation during or after the trial. All participants will continue to have regular access to public health and social services once the trial is over. The continuity of the intervention after the trial is dependent on mayoral discretion.

### Outcomes

The primary study outcome is child development at age 2 years as assessed by the PRIDI Scale. The secondary study outcome is child survival, which will be assessed using data from the municipality’s vital registration system (SIM and SINASC). Maternal depression will be assessed using the Center for Epidemiologic Studies Depression Scale (CES-D Scale).

Intention-to-treat analysis will be used to compare outcomes across the three study arms.

Additional per-protocol analysis will be conducted using data on program compliance. Our primary measure of compliance in the home-visiting arm will be the number of home visits completed. Our primary compliance measure in the center-based groups will be the number of sessions attended by the mother. Table 1 presents the data collection overview.

**Table 1 Tab1:** Data collection overview

Data collection phase	Instruments
Baseline (12,000)	Participant identification, anthropometrics, and habits Socioeconomic characteristics Household characterisits Previous gestational information Maternal depression (EPDS) Neighborhood characteristics and social support Couples’ conflict Parental knowledge Maternal cognitive development (WAIS) Paternal characteristics
Main endline (*N* = 3000)	Child development (PRIDI) – Primary outcome Maternal depression (CES-D) Caregiver self efficacy (PSOC) Parental style (ACT) Parental knowledge Child anthropometrics (height and weight)
In-depth endline assessment (*N* = 240)	Attachment and caregiver interactions (OMCI) Bayley Scales for Infant and Toddler Development (BSID-III)
Qualitative interviews	Focus groups with child development agents and group-meeting facilitators Individual interviews with program beneficiaries divided by full compliers, non-compliers, and dropouts by intervention study arm

*ACT*, *BSID-III* Bayley’s Scales for Infant and Toddler Development, *CES-D* Center for Epidemiologic Studies Depression Scale, *EPDS* Edinburgh Postnatal Depression Scale, *OMCI* Observation of Mother-child interaction, *PRIDI* Regional Project on Child Development Indicators, *PSOC* Parenting Sense of Competence Scale, *WAIS* Weschsler Adult Intelligence Scale

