### Recruitment

Recruitment for this project will be implemented in close collaboration with the Municipality Secretariat for Social Wellbeing and Health (SSWH). The SSWH identifies eligible pregnant women each month, and links them to the project team. Each woman is then visited by study staff and, conditional on their consent, completes a baseline interview. According to the municipality of Boa Vista, there are approximately 600 new pregnancies per month. The baseline forms are then used to establish eligibility for the program. As stated above, the following three (non-mutually exclusive) groups of women are eligible for the program:
Household classified as poorPregnant women under age 20 years (teenage pregnancies)Women with previous exposure to partner violence

In the first few years of the program, a small sample of women with children under age 1 year will also be enrolled. This sample will be used to assess the relative impact of reduced exposure to the interventions.

In order to achieve enrollment to reach the sample size, the research group hired and trained a team of interviewers that will visit the eligible participants from the municipality list, but also actively search for other potential participants in the field. The research team will use the municipality official birth records on a monthly basis to monitor any unenrolled new children born in the catchment areas and enroll them afterwards.

Given that we will have 12,000 participating households in the intervention, we do not foresee any difficulties reaching the 3000 sample-size target for the endline.

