### Statistical methods

For statistical analysis, standard regression models will be used for the continuous PRIDI outcome. Logistic regression models will be used for the secondary outcome of child mortality. All analysis will be conducted using the Stata 15 statistical software package. Primary analysis will be intention-to-treat. To assess the impact of partial compliance, we will also estimate average treatment effects on the treated (per-protocol analysis).

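### The program starts in pregnancy, but its mortality outcome starts at live birth, so fetal deaths it averts or causes go unseen and the infant mortality comparison may be somewhat distorted

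*Protocol article*

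**What the plan says.** **When the program starts.** The Background section explains that the intervention was moved earlier than in the São Paulo trial: "By enrolling pregnant women at the beginning of their third trimester", "with the ambition to increase health service utilization and reduce the risk of adverse birth outcomes". Trial design gives nearly the same starting point for the program as a whole: "from the end of the second trimester of pregnancy until the children reach age 3 years". Under Home visit arm (Arm 1), the pregnancy module is aimed at the period before delivery: "this module is designed to make mothers aware of pregnancy danger signs, to encourage adherence to antenatal care".

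**What is counted.** Mortality has three names:
- Abstract, Methods: "Secondary outcome will be infant mortality, which will be assessed linking municipal vital registration systems to the program rollout".
- Outcomes: "The secondary study outcome is child survival, which will be assessed using data from the" municipal registers (SIM and SINASC).
- Statistical methods: "Logistic regression models will be used for the secondary outcome of child mortality".

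Study setting gives the local infant mortality rate as 14.2 per 1000 live births. Neither the Abstract, nor Outcomes with its Table 1, nor Statistical methods names an outcome that counts fetal death.

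**The concern.** Exposure begins around the start of the third trimester, but the time at risk for the mortality outcome begins at live birth. Between the two lies an event that the program is meant to influence. Restricting the comparison to live births therefore conditions on something that happens after allocation and may depend on it.

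There are two consequences. First, a fetal death that the program averts is not credited, and one that it causes is not seen. Second, a fetus that survives to birth because of the program may be a fragile infant. If such infants die more often than others, they add deaths to the treated areas that have no counterpart in the control areas. An infant mortality benefit then looks smaller than it is, or in unfavourable cases becomes an apparent excess. The secondary result would not fully answer the survival part of the first specific objective.

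**Working it through.** **The plan's own figures.** The article gives no sample size or power for mortality, so there is none to reproduce. The usable inputs are 14.2 infant deaths per 1000 live births (Study setting) and about 12,000 anticipated baseline interviews (Sample size and power calculations). The 12,000 are interviews, not births, so counts built on them are approximate. The documents give no fetal death rate, no share averted and no death risk for infants so rescued; these are assumptions below.

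**Step 1: how much is left out.** Infant deaths: 12,000 × 0.0142 = 170. At an assumed 5 to 12 fetal deaths per 1000 after the program starts: 12,000 × 0.005 = 60 and 12,000 × 0.012 = 144. Share of fetal plus infant deaths not counted: 60/(60 + 170) = 26% and 144/(144 + 170) = 46%. These shares do not depend on the 12,000.

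**Step 2: when infant mortality rises despite a benefit.** Let s be the fetal deaths averted per 1000 live births and q the proportion of those infants who die. With no effect on other infants, the rate becomes

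(14.2 + s × q) / (1000 + s) × 1000.

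This exceeds 14.2 whenever q is above 0.0142, that is, whenever rescued infants die more often than the average infant.

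**Step 3: an illustration.** Assume 8 fetal deaths per 1000, 20% averted, and a quarter of those infants dying.
- Averted: 8 × 0.20 = 1.6 per 1000.
- Added infant deaths: 1.6 × 0.25 = 0.4 per 1000, or 0.4/14.2 = 2.8% of the infant mortality rate.
- Net change in fetal plus infant deaths: 1.6 − 0.4 = 1.2 per 1000 fewer.

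**Step 4: against sampling error.** Splitting 12,000 births evenly into two groups of 6,000, a simplification that favours precision, the standard error of a difference in infant mortality is

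sqrt(2 × 0.0142 × 0.9858 / 6000) = 0.00216, or about 2.2 per 1000, before any allowance for clustering.

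The shift in step 3 is 0.4/2.16 = 0.19 of a standard error.

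**Step 5: range.** The formula in step 2 was run with fetal deaths of 5, 10 or 15 per 1000 pregnancies, 10, 20, 30 or 50% averted, and 1, 5, 10, 30 or 50% of rescued infants dying: 60 combinations, all with no effect on other infants.

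| Case | Infant mortality per 1000 live births | Ratio to 14.2 | Fetal plus infant deaths per 1000 pregnancies |
|---|---|---|---|
| 10 per 1000, 30% averted, 30% die | 15.06 | 1.06 | 24.06 to 21.96 |
| 15 per 1000, 50% averted, 50% die (most extreme) | 17.87 | 1.26 | 28.99 to 25.24 |
| 15 per 1000, 50% averted, 1% die | 14.17 | 0.998 | 28.99 to 21.56 |

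In 53 of the 60 combinations the infant mortality ratio is 1.10 or less. Fetal plus infant deaths fall in all of them. In the first row a 6.1% reduction in deaths among other infants would cancel the rise; in the extreme row, 26%. In standard errors the rises are (15.06 − 14.2)/2.16 = 0.4 and (17.87 − 14.2)/2.16 = 1.7.

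**The case against.** **The outcome fits the stated objectives.** The Background rationale is neonatal death, the objectives speak of child survival and development, and infant mortality matches both. Adverse birth outcomes appear only as an ambition and are not defined as fetal death. A condensed article may also leave further birth outcomes to a fuller document. This stands in part: unlisted birth weight or gestational age is no fault in itself. It does not remove the point that the mortality outcome the article names begins after an event the program may change.

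**The effect is small and built on assumptions.** This largely stands. The illustration applies 20% averted to all pregnancies, although the sample size section expects 50% compliance; that implies 0.20/0.50 = 40% among compliers. It also allows no benefit to other infants, although the neonatal module targets newborn health, and a reduction of about 3% in their deaths would cancel the shift. A reader might infer that a successful program should be expected to show higher infant mortality. The documents do not support that: reversal is possible, not likely, and over most of the range would be hard to tell from noise.

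**The Outcomes sentence fixes no denominator.** Correct. It says only child survival. The start at live birth follows from the Abstract's term and from the rate in Study setting.

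**Late enrolment.** Under Recruitment, staff will use birth records to "monitor any unenrolled new children born in the catchment areas and enroll them afterwards". A reader might infer that such children, who enter alive, make the selection worse. That would hold only if survival were analysed among enrolled children, which the article does not say. Linking registers to the rollout, as in the Abstract, reads more naturally as all registered births and deaths by area and time, where date of enrolment does not affect who is counted.

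**Conclusion.** The concern holds in limited form. The program begins before birth with a stated hope for birth outcomes, while the only mortality outcome counts deaths after live birth, so fetal deaths averted or caused are invisible and the infant mortality comparison can be attenuated or, in unfavourable cases, reversed. At an assumed 5 to 12 fetal deaths per 1000, between 26% and 46% of fetal plus infant deaths would go uncounted. The distortion of infant mortality itself is unknown: about 0.4 per 1000 in the illustration, at most 10% of the rate in most assumed combinations, and up to 26% in the extreme one. All of this rests on rates that the documents do not give. The point concerns the secondary outcome only, and is an improvement worth making at low cost rather than a flaw that invalidates the survival analysis.

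**What to change.** - Keep infant mortality as named.
- Add a supplementary outcome: fetal death from the gestational age at which the program starts, plus infant death. Fix one gestational age for this purpose.
- Use all births (live births plus fetal deaths) in each of the 39 areas as denominator, taken in the same way in every area and classified by rollout timing, from the registration records already to be linked. The documents do not say whether those registers hold fetal deaths, so check this first and state how complete they are.
- Report gestational age and birth weight by arm where the linked birth record holds them.
- An analysis with women enrolled in pregnancy as denominator, excluding children first enrolled after birth, can serve as a sensitivity analysis only. Enrolment follows allocation and relies partly on active field search, and fetal deaths may be better ascertained where staff visit every fortnight than in control areas.

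The cost is one more outcome definition and an extension of a linkage already planned. The downside is some incompleteness in fetal death registration, which should be reported by area.

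### The per-protocol visit count is not restricted to PRIDI; used to define compliers for mortality it would make an ineffective program look protective, because death cuts the count short

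*Protocol article*

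**What the plan says.** The Outcomes section of the protocol article lists child development on PRIDI (primary), child survival from vital registration (secondary) and maternal depression. It assigns intention-to-treat to the comparison of outcomes across arms and continues: "Additional per-protocol analysis will be conducted using data on program compliance". Compliance is then defined for each platform: "Our primary measure of compliance in the home-visiting arm will be the number of home visits completed", and "Our primary compliance measure in the center-based groups will be the number of sessions attended by the mother". No cut-off, time window or outcome is attached to these counts.

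Statistical methods gives the PRIDI model and then the mortality model: "Logistic regression models will be used for the secondary outcome of child mortality". It adds "Primary analysis will be intention-to-treat" and says that, to assess partial compliance, "we will also estimate average treatment effects on the treated (per-protocol analysis"). This sentence follows both models and is not confined to PRIDI. The estimator is not named.

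On timing, the Background says most remaining infant mortality is neonatal, "with most deaths occurring in the first 7 days after birth". The home-visit section describes fortnightly visits with the child present, running to 36 months. The neonatal visits are set as follows: "One visit during the first week, a second visit at 15 days and the third visit at 28 days".

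**The concern.** A count of visits completed is a reasonable compliance measure for PRIDI, which is assessed in children alive at age 2. For mortality it is not, because the outcome ends the exposure. A child who dies in the first week can have at most one neonatal visit and no child-module visit, however willing the mother was. In the center arm such a child would usually have no postnatal session, since mothers are not expected to attend in the first two weeks. A high count therefore requires survival. This is immortal-time bias. It is separate from self-selection of mothers and arises even when attendance is unrelated to risk.

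At stake is the compliance analysis of the secondary outcome. Survival is part of the first study objective, and the results are meant to guide a national program. A protective effect, or a gradient with visits, that comes only from truncation would be easy to misread as benefit.

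**Working it through.** **The plan's own compliance arithmetic.** Sample size and power calculations assumes a 0.5 SD effect in compliant mothers and 50% compliance: 0.5 × 0.5 = 0.25 SD, as stated. This concerns PRIDI. No per-protocol figure is given for mortality.

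**Inputs from the article.** Infant mortality 14.2 per 1000 (Study setting); most deaths neonatal (Background); enrollment from the start of the third trimester (Background); fortnightly visits, three of them neonatal (home-visit arm).

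**Assumptions not in the article.** Six antenatal visits (about 12 weeks, fortnightly). A schedule to age 2 of 59 visits: 6 antenatal + 3 neonatal + 50 fortnightly. Deaths split over days 0–7, 7–28 and 28–365 as 50/20/30%, 60/20/20% or 35/15/50%. Attendance independent of risk, either half of mothers at 90% and half at 5%, or uniform with mean 50%.

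**Ceiling on the count.** A first-week death allows at most 6 + 1 = 7 visits; any neonatal death at most 6 + 3 = 9. A cut-off of 10 or more thus removes every neonatal death from the compliers.

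**Bound at 10 or more visits.** Let *d* be the risk of death, *n* the neonatal share of deaths, and *q* the chance that a mother whose child survives reaches the cut-off. Neonatal deaths reach it with probability 0, later deaths with probability at most *q*. With no program effect:

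- complier odds of death ≤ (1 − *n*)·*d*·*q* / [(1 − *d*)·*q*] = (1 − *n*)·*d*/(1 − *d*)
- control odds = *d*/(1 − *d*)
- odds ratio ≤ 1 − *n*

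For *n* = 0.5, 0.7 and 0.8 the ceiling is 0.50, 0.30 and 0.20.

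**Simulation.** Ineffective program, 4 million births per scenario, six scenarios (three death splits × two attendance patterns), compliers against controls at 14.2 per 1000:

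| Compliers defined as | False odds ratio, range |
|---|---|
| ≥ 1 visit | 0.70–0.93 |
| ≥ 3 | 0.65–0.77 |
| ≥ 6 | 0.34–0.81 |
| ≥ 9 | 0.12–0.48 |
| ≥ 14 | 0.08–0.36 |
| ≥ 29 (half of 59) | 0.005–0.03 |

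Worked line (50/20/30, high/low attendance, ≥ 9 visits): complier mortality is 4.07 per 1000, so the odds ratio is (4.07/995.93)/(14.2/985.8) = 0.284. At ≥ 29 visits it is (0.23/999.77)/(14.2/985.8) = 0.016. The bias need not grow steadily with the cut-off: in this scenario it is 0.65 at 3 visits, 0.76 at 6 and 0.28 at 9.

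With no cut-off at all, regressing death on the raw count within the treated arm gives an odds ratio of 0.82–0.95 per visit.

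**A different schedule.** A second simulation used 31 visits to age 1 and another attendance distribution with mean 50%. It gives risk ratios of 0.75, 0.39 and 0.19 at 3, 6 and 10 visits. At half the schedule the ratio is 0.12 (1.7 against 14.2 per 1000), or 0.17 with 40% of deaths in week 1 and 15% in days 8–28.

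**Alternatives under the same null (first simulation).**

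- Compliance from antenatal visits only (≥ 3 of 6): odds ratio 1.00–1.01.
- Intention-to-treat risk difference divided by compliance: −0.04 to 0.16 deaths per 1000, which is simulation noise.
- Share of visits offered while alive (≥ 50%): 0.99–1.07, so close to but not fully free of distortion.

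**The case against.** The best defense is that the article never says it will relate deaths to visit counts. The per-protocol sentences name no outcome, and the only numerical use of compliance concerns PRIDI. The abstract links vital registration to program rollout, which suggests an area-by-time exposure. The stated target, an effect on the treated, and the 0.5 × 50% = 0.25 SD reasoning both fit scaling the intention-to-treat effect by compliance. With no program effect the numerator is then zero and truncation does no harm. Cut-off, window and estimator belong in an analysis plan that is not shown.

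Much of this stands. The instrumental-variable reading is open, and missing detail is not the complaint. But the article does fix the compliance measure, lists survival among the outcomes just before it, and places the per-protocol sentence after the mortality model without restriction. It also labels the analysis per-protocol, a term often used for a complier-only comparison. Elsewhere it treats compliers as a group to be selected: the BSID-III subsample takes compliant mothers from the intervention arms and random mothers from the control group. Nothing stated prevents the same contrast for mortality.

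A reader might go further and infer that compliers survive by construction, so that a useless program would appear to save most infants. The documents do not support that as a general statement. They give no cut-off and no estimator, and at cut-offs reachable during pregnancy the false benefit can be modest.

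**Conclusion.** The concern holds in conditional form. The stated compliance measure is unsound for mortality if it is used to define compliers for comparison with controls, or as a regressor for death, and the article does not exclude either use. The false benefit is then partial at 1 to 3 visits (odds ratio about 0.65–0.93) and large from about 9 or 10 visits (about 0.1–0.5). At half the schedule it is near-total if visits are counted to age 2 (0.005–0.03), and the risk ratio is 0.12–0.17 if they are counted to age 1. These sizes rest on the assumed death timing, antenatal visit number, schedule and attendance. The direction rests only on the count stopping at death.

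The primary intention-to-treat analysis is not affected, nor is an instrumental-variable estimate when the program has no effect. The point should be settled before mortality is analyzed, but it does not threaten the main result.

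**What to change.** In Outcomes and Statistical methods, limit the visits- and sessions-completed compliance analysis to outcomes measured at the age-2 endline (PRIDI and maternal depression). For mortality, do one of the following:

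- report intention-to-treat only; or
- define compliance by something settled before the child is at risk, either program acceptance or contacts completed before birth, and estimate the effect with randomized assignment as the instrument, naming that estimator.

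Within the second option, program acceptance is the easier choice to defend. An instrument requires that assignment act only through the compliance variable, and a mother with few antenatal contacts may still receive postnatal visits.

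The cost is wording. No new fieldwork is implied, since attendance is already logged; the antenatal definition needs contacts dated relative to birth. What is given up is a dose-response analysis of mortality on postnatal visits, which truncation by death would make uninterpretable.
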